#### Physical activity

Accelerometry is an objective method of assessing free-moving physical activity, and is a well-established method for measuring activity in young children [52, 53]. The Actigraph GT3X+ activity monitor is a light (27 g) and small (3.8 cm × 3.7 cm × 1.8 cm) device. It is secured by a belt worn around the waist. The GT3X+ is capable of measuring accelerations from ~0.05 to 2 Gs and of capturing short epochs, allowing more accurate measurement of children’s physical activity [8, 54]. In line with existing recommendations, physical activity is monitored for 7 consecutive days [55] with removal of the device only when sleeping or prolonged exposure to water. Parents are asked to keep a diary, recording the time of day the accelerometer is placed on and taken off. Physical activity analysis will be conducted using ActiLife 6 software (ActiGraph, Pensacola, FL). Due to the short sporadic bursts of activity that are typical of young children, we will use 3 s epochs to accurately capture these short bouts of activity. The 2008 Evenson activity cut points for children will be used to determine levels of sedentary behaviour as well as time spent in light, moderate and vigorous intensity exercise. These established cut points have been validated in children aged 5–8 [56], and have been shown to have the highest accuracy in activity classification in children and adolescents aged 5–15 [57].

#### Questionnaires

Parents are asked to complete a questionnaire that asks questions about family demographics, measures of health and risk factors for obesity, and of participation in physical activity. In addition, a medical questionnaire is administered to confirm that the child has no contraindications to exercise. Parents also complete the Child Behaviour Checklist (CBCL) [58], which is used to assess behavioural (e.g. conduct problems), emotional problems (depression, anxiety) and autism-like behaviours [59]. The test-retest reliability of the CBCL scale scores range from 0.68 to 0.92 and reported classification accuracy ranges from 74 % to 84 % [60]. When appropriate (at age 6 years and older), parents will also complete the ADHD index of the Conners’ Parent Rating Scales, which covers diagnostic criteria in the DSM-IV [61]. Internal consistencies range from 0.85 to 0.94. Test-retest reliability ranges from 0.72 to 0.98 [61]. Given the young age of our cohort, we do not expect to see many cases of ADHD meeting DSM-IV diagnostic criteria at baseline. Thus, to obtain a reliable assessment of ADHD, we will administer the Conners’ twice over the course of the study (during years 2–4). Only children who meet criteria for ADHD based on the test [scores ≥6 (out of 9) on one or both subscales] at both times points will be identified as having ADHD. Each year the parents also complete the Developmental Coordination Disorder Questionnaire (DCD-Q), which is a measure used to identify motor coordination difficulties in children aged 5-15 [28].

#### Perceived self-efficacy

Perceived self-efficacy will be measured using the Perceived Efficacy and Goal Setting System (PEGS) [62]. PEGS uses colourful picture cards to illustrate essential tasks for participation in activities of daily living and school. These cards are presented to a child in pairs, with one picture demonstrating task competency and the other demonstrating less competence. The child then chooses which picture is more like him/her and then decides if he/she is ‘a lot’ or ‘a little’ like him/her. The scores for each item range from 1 (‘a lot like the less competent child’) to 4 (‘a lot like the more competent child’). The PEGS will be administered to children at all follow-up assessments.

#### Dietary intake

Parents complete a detailed food diary for 3 days (2 weekdays, 1 weekend day) recording the food and drinks consumed by their child for all meals and snacks noting brand names, quantities and preparation methods. The information provided will be analyzed to help interpret the relationship between body composition and dietary intake.

### Study protocol

#### Baseline testing – Phase 1

All eligible children are assessed in our laboratory to complete Phase 1 of baseline testing. At the baseline visit, parents complete all questionnaires and a semi-structured interview concerning the child’s ability to perform daily activities. The remainder of Phase 1 baseline testing includes assessments of motor skills (to determine presence of pDCD), cognitive ability (IQ), body composition, flexibility and standing long jump. Immediately following completion of the motor skill assessment, test results are scored and entered into a computer database. As mentioned previously, all children who score at or below the 16^th^ percentile on the M-ABC-2 as well as a random selection of children scoring above the 16^th^ percentile are invited into the longitudinal phase of the study and continue testing.

#### Baseline testing – Phase 2

For children selected to continue on to Phase 2 (i.e. longitudinal cohort), percent body fat, aerobic fitness, short-term muscle power output and foot structure are also assessed. At the end of Phase 2, an accelerometer to measure physical activity over the following 7 days is given to the child and any interested family members. An accelerometer logbook and 3-day food diary are also sent home with the family.

#### Testing years 2–4

All baseline assessments (excluding the IQ test) will be repeated once per year over the next 3 years. In addition, parents will complete the ADHD index (Conners) twice within the follow-up period and children’s self-efficacy to perform everyday tasks and activities will be assessed. In order to minimize attrition rates, we will provide parents with yearly reports that will highlight their child’s growth, physical activity, fitness and motor skills.

### Data analyses

To evaluate the stability of DCD over time, a straightforward descriptive analysis will be conducted. This will identify children whose scores change over time: those in the pDCD baseline group who, at a later assessment score above the 16^th^ percentile on the M-ABC-2 as well as those children in the control group whose measured performance declines to at or below the 16^th^ percentile, will be identified. At study end, children with 2 or more assessments differing from their baseline group assignment will be considered to have experienced substantial variability in motor proficiency. Depending on the numbers affected, they will either be used to form one or more additional groups in the analysis, or the analysis itself will be altered such that we retain baseline groups, but also model motor coordination as a time-varying characteristic.

To examine the association between DCD and fitness and adiposity, longitudinal growth models will be fitted with fixed effects for gender, baseline age, DCD status, ADHD symptoms (as these measures become available), time, and time by DCD. The outcomes will be total body fat, central body fat, aerobic fitness, and anaerobic fitness. First, these will be modeled as continuous, and then dichotomized at age-appropriate thresholds for overweight/obesity and inactivity, and fit additional models using the logistic link function. The time by group interaction will reveal the direction, magnitude, and significance of any divergence over time between the two groups. If we observe such a divergence, we will test whether it is mediated by physical activity by adding this measure to the above models. Finally, we will test the question of precedence using a distributed lag model in which each outcome is regressed on previous and contemporary measures of the predictors. This analysis will be repeated with a 3-group variable for DCD status that will differentiate among children who score at or below the 5^th^, those who score between the 6^th^ and the 16^th^, and those who score above the 16^th^ percentiles. This will allow us to assess whether the severity of motor impairment is associated with increased risk of poor fitness and overweight/obesity, and whether physical activity is a stronger mediator in the severe motor impairment group.

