## Methods/Design

### Study design

The CATCH study is a prospective cohort study with an initial cohort of 600 children aged 4 or 5 years at baseline: 300 with probable DCD (pDCD) and 300 controls. Using the Optimal Design software package [23], we have determined that an analysis with two groups of 300 assessed on 4 occasions will permit the detection of standardized effect size differences of approximately 0.3 with 80 % power and a significance level of 0.05. Taking expected attrition into account (~10 % per year), standardized effect sizes above approximately 0.35 will remain detectable. This means with 600 participants, we will be adequately powered to detect modest effect size differences between our two groups while accounting for loss to follow-up over time. The control group is randomly selected from the children completing the laboratory assessment who do not meet criteria for DCD. Data collection occurs at annual study visits, which include a motor coordination assessment, anthropometric assessments, and non-invasive physical fitness measures. All measures have previously been conducted successfully in this age group [24–26].

Through a parental interview, DCD questionnaire and demographic survey, parents provide additional information about their child’s performance of daily motor activities, demographics, measures of health and risk factors for obesity (adapted from surveys exploring these risk factors) and measures of participation in physical activity [27, 28]. The Hamilton Integrated Research Ethics Board has provided ethical approval for the study*.*

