#### Recruitment strategy

The sample is drawn from various community organizations and sites within the city of Hamilton, Ontario and surrounding area. These include parenting resource and support centres (e.g. Ontario Early Years Centres, Best Start programs), kindergarten classes in the public and Catholic school boards, among others.

Parents who provide their contact information via partnering community sites or contact the study team directly are telephoned by the research staff to determine their child’s eligibility and obtain informed, verbal consent. Eligible parents and children who provide verbal consent are invited to participate in the Phase 1 baseline laboratory visit. The recruitment process involves one randomization to select a proportion of Movement Assessment Battery for Children (M-ABC-2)-negative (typically developing) children into the control arm in the longitudinal study.

After Phase 1 of baseline testing, all children positive on the M-ABC-2 (pDCD) are recruited to the longitudinal study. Children who are negative on the M-ABC-2 are randomized to determine if they will continue onto Phase 2 (Fig. 1). Randomization probabilities are calculated to produce a sample of controls with a distribution of motor functioning that matches the population distribution of non-cases.

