#### Assembling the study cohort at baseline

As noted previously, we will assemble a cohort of 600 children for the longitudinal portion of the study: 300 children meeting criteria for pDCD (see below) and 300 typically developing children. This approach will provide a balanced sample, which maximizes statistical power at a given sample size. We will use random sampling rather than matching because this approach ensures that this group is representative of typically developing children with respect to both measured and unmeasured variables [29].

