#### Defining cases of pDCD

We will define cases based, in part, on the 2011 European Academy of Childhood Disability (EACD) Guidelines for Identification of Children with DCD [30], which require: (1) a score at or below the 16^th^ percentile on a standardized measure of motor impairment (M-ABC-2) [31]; (2) evidence of impact on daily function; (3) IQ score above 70 (KBIT-2) [32]; (4) absence of any medical condition affecting motor functioning (parent reported). In addition, we have also decided to exclude children whose birth weight is less than 1500 grams, as children with very low birth weight are apt to present with a variety of co-morbid health problems that may affect motor coordination. The EACD guidelines also recommend repeated measurement of motor function in children under 6 years of age to ensure valid and reliable identification of children with DCD, which we will also do.

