### Measurements

#### Motor coordination

A standardized motor coordination assessment is conducted in order to identify children with pDCD. We are using the Movement Assessment Battery for Children 2^nd^ Edition (M-ABC-2), the most widely used assessment for the identification of DCD [26, 33, 34]. The M-ABC-2 is an individually administered standardized test which includes 8 motor tasks within 3 categories: Manual Dexterity; Aiming & Catching; and Balance (static and dynamic). Raw scores on these items are converted into standard scores based on the child’s age, and then converted into an overall percentile. Test-retest reliability and standard of error of measurement for the total test scores have been reported to be 0.80 and 1.34, respectively [31]. Studies have shown that the M-ABC-2 is a reliable and valid tool for the assessment of movement difficulties, even in very young children (4 to 6 years of age) [31].

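### The stability rule reads two or more crossings of the 16th-percentile cut as motor change without allowing for measurement error; with no true change it would still flag about 37% of pDCD children and 5% of controls in the base case

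*Protocol article*

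**What the plan says.** All places are in the protocol article.

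- **Entry to the groups.** Recruitment strategy: "After Phase 1 of baseline testing, all children positive on the M-ABC-2 (pDCD) are recruited to the longitudinal study". Baseline testing – Phase 1 says the same: children at or below the 16th percentile, plus a random selection of those above it, go forward on the score from that visit.
- **Follow-up.** Testing years 2–4: "All baseline assessments (excluding the IQ test) will be repeated once per year over the next 3 years". That gives three later M-ABC-2 results.
- **The stability rule.** Data analyses calls the analysis descriptive and identifies children whose later score falls on the other side of the 16th percentile. Once all visits are in, the rule is this: "children with 2 or more assessments differing from their baseline group assignment will be considered to have experienced substantial variability in motor proficiency".
- **What follows from a flag.** According to how many children are affected, they either form one or more extra groups in the analysis, or the baseline groups are kept and motor coordination is modelled as time-varying.
- **Precision of the test.** Motor coordination: "Test-retest reliability and standard of error of measurement for the total test scores have been reported to be 0.80 and 1.34, respectively".
- **Repeat testing.** Defining cases of pDCD: "The EACD guidelines also recommend repeated measurement of motor function in children under 6 years of age to ensure valid and reliable identification". The sentence goes on to commit the study to this, but no section says how repeats would confirm or revise the baseline group.

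**The concern.** A group chosen because one imperfect score was low will score higher on average when retested, even if no child has changed. Some of its members have a true score above the cut and had a poor day at baseline. The rule compares three later scores with that selecting score, and it calls two disagreements variability in motor proficiency. It uses neither the reliability nor the standard error of measurement (SEM) that the protocol itself reports.

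The effect is also uneven. Controls come from the much wider range above the cut, so few of them cross it by chance. The same measurement error would therefore make pDCD look changeable and typical development look steady.

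Two things are at stake. For the first objective, error could be described as motor change. For the second, the number flagged decides whether new analysis groups are formed or the model is altered, so error could reshape the fitness and adiposity analysis. The time-varying alternative uses the same error-prone score and does not correct for it.

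**Working it through.** The protocol gives no expected share of flagged children, so there is no figure of its own to reproduce.

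**Inputs from the protocol:** cut at the 16th percentile (z = −0.994); reliability 0.80; SEM 1.34; one baseline and three follow-up tests; 300 children per group; attrition of about 10% per year.

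**Assumptions not in the protocol:** normal scores; recruits follow the test norms; errors independent between visits with constant variance; no child's true score changes.

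**Consistency check.** SEM = SD × √(1 − reliability), so SD = 1.34 / √0.20 = 3.00. The two stated precision figures agree.

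**Model.** On a scale with total variance 1, the true score is T ~ N(0, 0.80) and each observed score is T plus error ~ N(0, 0.20). Given T = t, the chance of scoring at or below the cut is b(t) = Φ((−0.994 − t)/√0.20), and the chance of scoring above it is a(t) = 1 − b(t).

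- P(at least 2 of 3 follow-ups above the cut | pDCD at baseline) = E[b(3a²b + a³)] / E[b], with E[b] = 0.16.
- P(at least 2 of 3 at or below the cut | control at baseline) = E[a(3b²a + b³)] / E[a], with E[a] = 0.84.

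**Base case, by numerical integration:**

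| Quantity | pDCD | Controls |
|---|---|---|
| Across the cut at any one follow-up | 38.4% | 7.3% |
| Flagged (2 or more of 3) | 37.0% | 5.4% |
| Flagged, out of 300 | 111 | 16 |

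Simulation of 3 million children gives the same flagged share for pDCD (37.0%).

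**By reliability (flagged):**

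| Reliability | pDCD | Controls |
|---|---|---|
| 0.70 | 46.6% | 6.3% |
| 0.80 | 37.0% | 5.4% |
| 0.90 | 25.2% | 4.0% |
| 0.95 | 17.4% | 2.9% |

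**If recruits average below the norm (reliability 0.80):**

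| Shift | pDCD | Controls |
|---|---|---|
| −0.25 SD | 31.8% | 7.7% |
| −0.50 SD | 26.8% | 10.5% |
| −0.75 SD | 22.0% | 13.9% |
| −1.00 SD | 17.7% | 17.9% |

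**Attrition.** With 10% loss each year, 0.9³ = 72.9% have three follow-ups and 0.9² × 0.1 = 8.1% have exactly two. For a child with only two follow-ups, the chance that both are discordant is 23.6% (pDCD) or 2.8% (controls). Over all enrolled children:

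- pDCD: 0.729 × 37.0% + 0.081 × 23.6% = 28.9%
- controls: 0.729 × 5.4% + 0.081 × 2.8% = 4.1%

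**Who is flagged (base case).** 35.5% of the pDCD group have a true score above the cut, and they make up 76% of the flagged pDCD children. The rule flags 79% of them. It also flags 14% of pDCD children whose true score is at or below the cut, which is 0.645 × 13.7% = about 9% of the group.

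**The case against.** **The count answers the stated hypothesis.** The first objective predicts that children meeting criteria at baseline will go on meeting them. That is persistence of classification, and crossing counts measure it directly. This stands. The fault lies in calling the crossings variability in motor proficiency, not in counting them.

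**Nothing is decided by the count.** The analysis is descriptive, with no test and no share at which DCD is declared unstable. A reader might infer that the study is bound to report DCD as unstable and contradict its own hypothesis. The protocol does not say that the flagged share settles the question, so that reading goes too far. The flag does still feed the choice of groups and model for the second objective.

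**The rule does useful work.** Requiring two discordant results instead of one lowers the flagged share in pDCD from 61% to 37%. Most of those flagged were misclassified at baseline, and among unflagged pDCD children 88% are truly at or below the cut, against 64% before flagging. This stands too. It is a reason to describe flagged children as possible misclassification, which the present wording does not do.

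**About a third is not a settled figure.** It is one base case. Case definition also lists functional impact, while the recruitment text admits on the score alone. If impact were required as well, the share would be about 20–31% (assumed correlation of impact with the true motor score 0.3–0.7, assumed prevalence of impact 10–25%).

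**Denominator.** A reader might also object that children with fewer than two follow-ups can never be flagged yet stay in the denominator. The protocol states no denominator, and a condensed article may leave that to the full plan, so this is not an error in the text.

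**Conclusion.** The concern holds as a fault of classification and interpretation, not of type I error. Applied as written, the rule labels measurement error as motor change. At the protocol's reliability, with scores following the norms, independent errors and no true change, about 37% of pDCD and 5% of controls would be flagged. The size depends on those assumptions: 17–47% of pDCD over reliability 0.95–0.70, and 27% against 11% if recruits average 0.5 SD below the norm. The imbalance between groups disappears at 1 SD below, where both are about 18%. In none of the cases examined is the pDCD share negligible. Because the analysis is descriptive and its counts remain valid as persistence of classification, this should be fixed but is not fatal to the objective.

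**What to change.** 1. Keep the crossing counts, described as persistence of classification.
2. Print beside them, by group, the counts expected under no true change at reliability 0.80, with a sensitivity range for reliability and for the motor level of the recruited children. Interpret only the excess as motor change.
3. Support this with a longitudinal mixed model of the continuous M-ABC-2 standard score that separates visit-to-visit error from child-level change. Estimate the error variance, or compare it with the SEM of 1.34; do not fix it there, because the protocol does not give the retest interval behind that figure and the visits are a year apart.
4. Do not form additional groups for the fitness and adiposity models on the raw flag count alone.
5. Describe flagged children as possible baseline misclassification or change.

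The cost is new wording in the analysis plan, a short calculation and one further model, all on data already planned. The stability statement will be softer.

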Specifically, our objectives are:To examine the stability of DCD over time. We hypothesize that children who meet study criteria for DCD at baseline will continue to meet criteria for DCD at follow-up assessments, and that children who do not meet study criteria for DCD at baseline will not meet criteria in later assessments.To evaluate the precedence of DCD, fitness and adiposity. We hypothesize that children who meet criteria for DCD at baseline will, over time, show decreasing aerobic and anaerobic fitness and increasing weight (Body Mass Index [BMI], body fat percentage and waist circumference) relative to children who are typically developing. This divergence will be partially mediated by differences in physical activity.

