## Discussion

DCD is a highly prevalent chronic health condition, the impact of which has remained largely unrecognized. Given the significant number of children affected as well as how many of these same children show high rates of inactivity, poor fitness and obesity, it is essential that we better understand possible causal pathways between DCD and these aspects of physical health. To date, our studies have conclusively shown that many children identified with motor coordination problems in the general population are already unfit and overweight by the time they reach middle school. In order to fully understand these pathways, a longitudinal study beginning during a developmental period in which motor deficits are apparent but physical fitness has not yet deteriorated and obesity may not have yet developed, is required.

The CATCH study will be the first study to examine the longitudinal relationships among motor coordination, physical activity, fitness and adiposity from early to middle childhood.

It is essential to elucidate these relationships because the direction of these associations will help to determine the types of interventions children with DCD require. In some children, the presence of obesity and inactivity may lead to underdeveloped motor skills and poor fitness [63, 64]; for these children, interventions promoting physical activity and healthy diets may be appropriate. However, children with a diagnosis of DCD have fundamental motor impairments; thus, in these cases, a public health intervention targeting physical activity – the behaviour affected by the underlying disability – may be ineffective, and may even cause injury and/or be harmful to children’s self-esteem. For these children, a simultaneous effort must be made to adapt instructional methods and physical activity programs to accommodate their motor challenges [65]. It is therefore imperative that we understand the causal ordering in order to intervene in a manner that will address the actual problem.

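### The plan lets follow-up M-ABC-2 scores redraw the comparison groups and does not keep the baseline-group contrast primary, so the divergence test can be biased if weight gain or lost fitness lowers motor scores

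*Protocol article*

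**What the plan says.** Hypothesis 2 (Background, objectives) is framed on status at entry: "children who meet criteria for DCD at baseline will, over time, show decreasing aerobic and anaerobic fitness and increasing weight", relative to typically developing children. The test is the interaction in the growth models (Data analyses): "The time by group interaction will reveal the direction, magnitude, and significance of any divergence over time between the two groups".

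The same section defines a switcher, in terms of motor proficiency, from follow-up scores: "At study end, children with 2 or more assessments differing from their baseline group assignment will be considered to have experienced substantial variability in motor" […]. Two courses are then open. One is: "Depending on the numbers affected, they will either be used to form one or more additional groups in the analysis". The other is that "the analysis itself will be altered such that we retain baseline groups, but also model motor coordination as a time-varying characteristic".

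The scores that define switching are collected alongside the outcomes. Testing years 2–4 states: "All baseline assessments (excluding the IQ test) will be repeated once per year over the next 3 years". On the direction of effect, the Discussion says that in some children "the presence of obesity and inactivity may lead to underdeveloped motor skills and poor fitness".

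The article nowhere says that the model with unaltered baseline groups remains the primary test if either course is taken.

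**The concern.** A group built from year 2 to 4 motor scores is not a baseline exposure. Once switchers move to their own groups, the remaining contrast is between children who stayed at or below the cut and children who stayed above it. If faster fat gain or loss of fitness lowers later M-ABC-2 scores, pDCD children with poor outcome trajectories tend to stay in pDCD, and those with good trajectories tend to move out. Among controls the reverse happens. Both movements push the remaining groups apart in the direction that hypothesis 2 predicts, even if baseline motor status has no effect on the trajectory.

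The second course keeps baseline groups but adds post-baseline motor scores, so its interaction term is not the plain baseline contrast either.

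At stake is the study's central question. The article presents CATCH as a study of which factor comes first, and this step could let the reverse path enter the exposure and be read as the forward path.

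**Working it through.** **Inputs from the protocol article.** 300 children per group, 4 occasions, significance level 0.05 (taken as two-sided), 80% power, detectable effect about 0.3, or about 0.35 after roughly 10% attrition per year (Study design); M-ABC-2 reliability 0.80 (Motor coordination); cut at the 16th percentile (Defining cases of pDCD); switcher = at least 2 of the 3 follow-ups discordant (Data analyses).

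**The plan's own figure.** For a linear slope over 4 annual visits, the centred times have sum of squares 5, so the detectable effect in slope SD is (1.960 + 0.842) × √[(2/300) × (1 + R/5)]. R is the residual variance divided by the slope variance, which the article does not give. R = 0 gives 0.229. An effect of 0.30 needs R = 5 × [(0.30/0.2287)² − 1] ≈ 3.6. The step to 0.35 follows: 300 × 0.9³ = 218.7, and 0.30 × √(300/218.7) = 0.351. The 0.3 is attainable but cannot be confirmed. The point does not depend on it.

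**How many children the rule could catch.** With reliability 0.80 and a true motor score that never changes, about 37% of cases and 5% of controls meet the switcher rule through measurement error alone. With 10% loss per year, 10% + 0.9 × 10% = 19% have fewer than two follow-ups and can never be classed as switchers. No bias from this last feature has been shown.

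**Null simulation, model A.** The outcome slope is independent of the baseline motor score, so there is no true divergence. Follow-up M-ABC-2 = true score − k × slope × t/3 + error, with the slope in SD units and t = 1, 2, 3. Thus k is the motor SD lost by year 4 per SD of faster fat gain. Each child's slope is estimated with error of about 0.7 slope SD. Groups are compared by a z-test on slopes.

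| k (assumed) | False divergence, no attrition (slope SD) | Rejection, no attrition | Rejection, 10% yearly loss |
|---|---|---|---|
| 0 | 0 | about 5% | about 5% |
| 0.1 | – | 11% | 7–10% |
| 0.2 | 0.16 | 27% | 19% |
| 0.3 | 0.23 | 54% | 37% |
| 0.5 | 0.37 | 90% | 72% |

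The last two columns are for the groups left after switchers move out. Unaltered baseline groups reject in about 3–6% throughout. Independent runs with attrition gave 17–20%, 30–37% and 65–72% at k = 0.2, 0.3 and 0.5. One of them put the false divergence at about 0.11, 0.16 and 0.26; it is somewhat larger if children with no follow-up are left out.

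**Null simulation, model B.** Slope SD 0.15, residual SD 0.5, motor slope SD 0 or 0.15, no attrition.
- Motor change unrelated to outcome change: no bias, rejection 4.7–5.9%.
- Motor slope correlated with outcome slope at 0.2, 0.3, 0.5: false divergence 0.07, 0.09, 0.17 slope SD; rejection 6.2%, 8.9%, 17.6%.
- Outcome change feeding into the M-ABC-2 at 0.25, 0.5, 1.0 motor SD per outcome unit: false divergence from 0.08 up to 0.33 slope SD; rejection 7–9%, 16–19%, 45–52%.
- Unaltered baseline groups: 4.0–5.9%.

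**Why A and B differ.** On A's scale, B's strongest feedback is 1.0 × 0.15 × 3 = 0.45, so the feedback is similar. B has noisier slopes: (0.5/√5)/0.15 = 1.49 slope SD of estimation error against 0.7. In terms of R, A has 5 × 0.7² = 2.45 and B has 0.5²/0.15² = 11.1. The two lie either side of the 3.6 that the plan's 0.3 would imply if that effect is in slope SD, which the article does not say.

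**The case against.** The strongest reply is that re-grouping repairs misclassification. The article notes, under Defining cases of pDCD, that guidelines recommend repeated motor testing under age 6 for valid identification, and says the study will do this. If divergence belongs only to children truly below the cut, the baseline contrast recovers about 61–67% of it and the contrast without switchers about 87–91% (classical error, two definitions of the true cut). Under pure measurement error re-grouping adds no false divergence. This stands. It means the switcher analysis should be kept, not struck out.

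Second, re-grouping is one of two courses, switchers are not dropped, and precedence is also examined with a distributed lag model. All true. But removing switchers from their original groups is itself what changes the remaining contrast, and no sentence keeps the plain baseline model primary.

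Third, a reader might infer that the choice of course follows the outcome results. The text does not support this: the trigger is how many children change motor category. The absence of a numerical threshold is a detail that a condensed article may leave to the full plan, and it is not part of this point.

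Fourth, a reader might take the article to call the reverse path equally plausible. That wording in the Background concerns low strength, endurance and obesity as features of the developmental syndrome. The support for the reverse path is the more guarded Discussion sentence about some children.

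**Conclusion.** The point holds as a risk that the plan leaves open. The rule as written can replace a baseline exposure with one that uses motor scores from the outcome period, and any resulting bias favours the hypothesis. Its size rests on assumptions: there is none when motor change is unrelated to outcome change. With feedback of k = 0.1 to 0.5, false rejection is roughly 10% to 72% with 10% yearly attrition and about 11% to 90% without. Other variance assumptions give 6% to 52%. Baseline groups stay near 5%.

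Two stronger readings are not supported. One is that the plan will produce a false divergence: the feedback strength appears nowhere in the document, and the re-grouping course may not be taken. The other is that the false effect matches the 0.3 the study is sized for: without attrition model A passes 0.3 only at k = 0.5, model B only at its strongest feedback, and the article does not define the unit of its 0.3.

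**What to change.** State in Data analyses that the time-by-baseline-DCD interaction, estimated in the baseline groups without post-baseline motor terms, is the primary test of hypothesis 2 whatever number of children change category. Report both of the present options as prespecified secondary or sensitivity analyses: the switcher-group model, and the model with time-varying M-ABC-2, with the score entered from the previous wave.

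The cost is about one sentence and no new data. The real downside is dilution: children misclassified at baseline remain in their baseline group in the primary test, which will understate a true divergence. Setting the switcher-group result beside it shows how far the two differ, with the caution that a larger divergence there may reflect corrected misclassification, reverse causation or both.
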